### Data collection and follow-up

All data will be recorded from an electronic case report form (eCRF) specifically elaborated for the study (eCRF CleanWEB, Telemedicine Technologies S.A.S., www.tentelemed.com, 2015) and will be recorded at four specific study’s times as follows: randomization (T0), baseline assessment (T1), delivery (T2), and at 6 months after delivery (T3). All assessments are based either on medical files (pregnancy and delivery characteristics, obstetrical and neonatal outcomes), face-to-face questionnaires (smoking and alcohol habits, personal hygiene, pregnancies history or symptoms, and concomitant treatments such as treatment with pessary or progesterone), phone calls (to collect data on vaginal symptoms or potential side-effects of antibiotic) or self-report (health outcomes of their infant and health service use during the 6 months following the initial hospitalization). Details of the data recorded at the different times of the study are given in Table 3.

**Table 3 Tab3:** Data collection, instruments and assessment times

At randomization (T0)	Data on the health status of the participant and pregnancy characteristics will be collected from medical files of the practitioners. A face-to-face questionnaire will be also completed by all women and filled out by the midwife/obstetrician to collect specific data on demographics characteristics, smoking and alcohol habits, previous pregnancies and personal hygiene. The first vaginal swab will be collected by the practitioner and send to one of the two point-of-care laboratories associated to the study.
At baseline assessment – (during screening and treatment phases - T1)	Subsequent vaginal swabs will be realized during either routine pregnancy consultation or at the woman’s home depending on each participant schedule. In this later case, the sample will be sent by the women to the referent POC laboratory using a stamped, self-addressed envelope. Symptoms and potential side effects of antibiotics will be collected via a telephone interview. Participants will be informed via a phone call for subsequent vaginal swabs and treatment intake if needed.
At delivery (T2)	All relevant clinical and obstetrical outcomes during pregnancy will be collected from the medical files. To complete data collection, a face-to-face interview with women around delivery phase will be scheduled. All relevant data such as pregnancy complications, hospitalizations, delivery characteristics (including birth weight, terms at delivery, or fetal death) will be collected.
At 6 months after delivery (T3)	Participants will be provided with a questionnaire, on which they will be asked to record all health outcomes of their infant and associated health service use.

### Pharmaceutical aspects

Experimental drugs, azithromycin 250 mg oral tablets (ZITHROMAX™) and amoxicillin 500 mg oral capsules (CLAMOXYL™), will be packaged and labeled by the “Unité d’Expertise Pharmaceutique et Recherche Biomedicale” pharmaceutical unit of the Hospital Pharmacy of AP-HM and distributed to the dispensing hospital pharmacy of each investigating center. At the end of the study, used and unused treatments will be returned to the dispensing pharmacy and destroyed.

### Sample size

The sample size was calculated from the expected differential ICER per preterm birth avoided between the two groups. In accordance with Briggs [22], the following hypothesis is stated: with an expected incremental rate of preterm birth of 1.3 % (4.3 % in the control group [23] and 3.0 % in the experimental group), an expected incremental cost of 230 euros (including cost of initial and following point-of-care tests and cost of treatments for 10 % of the women [24]), and an expected differential ICER at 22,500 euros corresponding to the avoided cost of a preterm birth before 37 weeks [25], with an 80 % statistical power and a threshold for statistical significance set at a *P* value of 0.05, and assuming that a potential 20 % of patients will be lost to follow-up, these calculations showed that 6,800 patients are needed (3,400 per group). Considering the potential of inclusion of each participating center, the inclusion duration will be planned over a 12-month period. The maximal period of participation for the included women is 12 months.

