### Randomization

Computer-generated randomized lists were drawn up before the beginning of the study, using a permuted block design, under the responsibility of the clinical research unit (AP-HM). The randomization was stratified by center (1:1 allocation ratio).

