### Statistical analysis

The data will be analyzed using SPSS version 20.0 software. Statistical significance is defined as *P* < 0.05. The methodology will be based on the Consolidated Standards of Reporting Trials Statement (CONSORT, http://www.consort-statement.org/consort-statement/) [26]. The full analysis population (including all subjects who will be randomized and will be at least evaluated at baseline) will be used in the primary analysis and the per protocol population (including all subjects who will be randomized and will not have major protocol deviations) will be used in the secondary analysis to assess the reliability of the results. Finally, missing data will be handled where possible using multiple imputations, and a sensitivity analysis will be performed. No interim analysis is planned.

The normality of the parameters will be estimated using frequency histograms and the Shapiro test. In case of nonparametric distribution, the data will be log transformed to obtain a normal distribution or nonparametric bootstrapping performed for cost data. In accordance with the distribution of the parameters, the baseline parameters will be presented separately for the control group and the experimental group: mean (standard deviation) or median (interquartile range) for continuous variables, proportions for categorical variables. Then, data will be compared between the two groups using Student’s t-test for continuous variables (durations), and chi-square or Fisher’s exact tests for categorical variables.

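### The inputs of the ICER hypothesis do not give 6,800; the number matches a comparison of preterm-birth rates, with about 72% power two-sided or 80–82% one-sided after 20% loss

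*Protocol article*

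**What the plan says.** The Sample size section names its basis: "The sample size was calculated from the expected differential ICER per preterm birth avoided between the two groups". Its inputs are preterm-birth rates of "4.3 % in the control group [23] and 3.0 % in the experimental group", an incremental cost of 230 euros, a value of 22,500 euros that is labelled the expected differential ICER and also tied to the avoided cost of a preterm birth, "with an 80 % statistical power", "a threshold for statistical significance set at a *P* value of 0.05", and 20% loss to follow-up. It concludes that "these calculations showed that 6,800 patients are needed (3,400 per group"). The method is given only by citation. No sidedness, cost standard deviation or cost–effect correlation is stated.

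Under Statistical analysis, "Statistical significance is defined as" P < 0.05, and groups are compared with "chi-square or Fisher’s exact tests for categorical variables". Under Randomization, "The randomization was stratified by center (1:1 allocation ratio"). The primary endpoint is the ICER per preterm birth avoided before 37 weeks. The Cost-effectiveness analysis section plans bootstrapping and acceptability curves.

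**The concern.** The section presents a derivation with a definite result, so it can be checked. Two things look wrong. First, the listed cost and effect give an ICER different from the one listed beside them. Second, a net benefit as small as these inputs imply should need far more than 6,800 women, while 6,800 is close to what an ordinary comparison of 4.3% with 3.0% would need.

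At stake is how the result is read. If the article is taken at its word, the primary cost-effectiveness endpoint has 80% power, and an equivocal ICER would look like the answer of an adequately sized trial.

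**Working it through.** **Inputs.** From Sample size: p1 = 0.043, p2 = 0.030, d = 0.013, incremental cost 230 euros, 22,500 euros per preterm birth, power 80%, P = 0.05, loss 20%. From Randomization: 1:1 allocation. Evaluable per group: 3,400 × 0.8 = 2,720. Variance sum: 0.043 × 0.957 + 0.030 × 0.970 = 0.07025. The pooled rate is 0.0365, so 2 × 0.0365 × 0.9635 = 0.07034.

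**1. Reproducing 6,800 as a comparison of rates.**

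n = [z(α)·√0.07034 + 0.8416·√0.07025]² / 0.013²; continuity-corrected n' = (n/4)·[1 + √(1 + 4/(n·d))]².

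| Test at 5% | n per group | corrected n' | n/0.8 | n'/0.8 |
|---|---|---|---|---|
| One-sided (z = 1.645) | 2,573 | 2,724 | 3,216 | **3,405** |
| Two-sided (z = 1.960) | 3,266 | **3,418** | 4,082.5 | 4,272.5 |

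Two cells match 3,400: one-sided with the 20% loss (total 6,810), and two-sided with no loss allowance (total 6,836). The first uses a sidedness that the article does not declare; the second drops the stated loss. Neither uses the 230 or the 22,500 euros.

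**2. Power of the rates comparison.** Power = Φ{[0.013·√n − z(α)·√0.07034] / √0.07025}.

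- 2,720 per group, two-sided: 72.5% (70.0% continuity-corrected).
- 2,720 per group, one-sided: 81.9% (79.9% continuity-corrected).
- 3,400 per group (no loss), two-sided: 81.6%.

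Two-sided 80% power with 20% loss needs 2 × 4,082.5 = about 8,165 women.

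**3. The ICER hypothesis.** The inputs give 230/0.013 = 17,692 euros. For 22,500 to be the expected ICER, the incremental cost would have to be 22,500 × 0.013 = 292.5 euros, not 230. Read as a ceiling, 22,500 gives a net benefit of 292.5 − 230 = 62.5 euros per woman.

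With cost variance set to zero (an assumption):

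- SE = 22,500 × √(0.07025/2,720) = 114.3 euros; z = 62.5/114.3 = 0.55.
- Power: Φ(0.55 − 1.96) = about 8% two-sided; Φ(0.55 − 1.645) = about 14% one-sided.
- With no loss (3,400 per group): about 9% and 15%.
- For 80%: (1.960 + 0.8416)² × 22,500² × 0.07025 / 62.5² = about 71,500 evaluable per group two-sided, or about 56,300 one-sided.

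**4. Range over what is not stated.** With cost SD c and correlation ρ between cost and avoided preterm birth, each group contributes 22,500²·p·q + c² − 2ρ·22,500·√(p·q)·c to the variance, and SE² is the sum over the two groups divided by 2,720. All c and ρ below are assumptions.

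- c = 3,000, ρ = 0: SE 140, power 6.5% two-sided, 11.5% one-sided.
- c = 5,000, ρ = −0.5: SE 217, power about 5% and 9%.
- c = 3,000, ρ = +0.9: power about 21% and 31%.
- c = 5,000, ρ = +0.9: power about 18% and 27–28%.
- Between these two SDs, power at ρ = +0.9 peaks near c = 3,800: SE = √[(4.05 + 2.92) million/2,720] = 50.6, z = 1.235, power about 23% and 34%.

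If the neonatal saving is also credited inside the cost, net benefit is 292.5 + 292.5 − 230 = 355 euros. With no other cost variance, SE = 2 × 114.3 = 228.7 and z = 1.55, giving about 34% two-sided and 46% one-sided.

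**5. Expected precision at 2,720 per group.** Risk difference: 1.96 × √(0.07025/2,720) = 1.0 percentage point. Net benefit at 22,500 with zero cost variance: 1.96 × 114.3 = about 224 euros.

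**The case against.** The best defence is that the article fixes no sidedness. A one-sided 5% comparison of rates with continuity correction and the stated loss gives 6,810, so the number may be a correct one-sided calculation, described badly. This stands: 6,800 cannot be called an arithmetic error for the rates. Two-sided is only the usual reading of a chi-square or Fisher test at P < 0.05.

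Second, the 20% loss may not fall on the delivery outcome. Gestational age comes from medical files at delivery, whereas the step that depends on participants returning a questionnaire is six months later. Two-sided power is 75% at 15% loss, 77% at 10% and 80% at 4%. Even so, 20% is the article's own planning figure.

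Third, the net-benefit test is my reading: the article does not name it, calls 22,500 the expected ICER, and rests the method on a citation. This also stands, and it is why the ICER figures carry conditions. It does not rescue the claim, because no variant tried comes near 80%, and the most favourable correlation requires costs to be higher in women who avoid preterm birth, against the article's premise that preterm birth is costly.

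Fourth, the article describes no significance test of the ICER; bootstrap and acceptability curves already display uncertainty. This limits the harm to interpretation and makes the repair easy, but the stated power remains unsupported.

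**Conclusion.** The stated basis of the sample size does not produce the stated number. On the article's inputs, with 22,500 euros as a ceiling, 20% loss and zero cost variance, power for the ICER hypothesis is about 8% two-sided or 14% one-sided. The most favourable alternative examined, crediting neonatal savings with no other cost variance, gives 34% or 46%. The figure of 3,400 per group reproduces as a comparison of preterm-birth rates, for which power after the stated loss is about 72% two-sided (70% continuity-corrected) or 80–82% one-sided.

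A reader might go further and infer any of the following; the document does not support them.

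- That 6,800 is flatly too small for the rates: a one-sided 5% test reaches 80%.
- That no two-sided reading reaches 80%: without loss, 3,400 per group has 81.6%.
- That ICER power is below 10% without qualification: this needs a two-sided test, 22,500 as the ceiling, and cost assumptions that the article does not give.
- That any cost variance must lower power or widen the interval: a strong positive cost–effect correlation does the opposite.

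**What to change.** Keep 6,800 and change the text.

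1. State that 6,800 rests on the comparison of preterm-birth rates (4.3% v 3.0%). Give the sidedness and the matching power after 20% loss: about 72% if two-sided, or about 80% if one-sided 5% was intended.
2. Reconcile 22,500 euros with the implied 17,692 euros, and say whether 22,500 is an expected ICER or a ceiling.
3. Withdraw the 80% power claim for the ICER, unless a calculation with stated method, cost SD and cost–effect correlation supports it.
4. Present cost-effectiveness as estimation through the bootstrap and acceptability curves already planned. Give the expected 95% half-widths: about 1.0 percentage point for the risk difference, and about 224 euros per woman for net benefit at 22,500 if cost variance is zero (wider under zero or negative cost–effect correlation).

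The cost is wording only. Recruitment, conduct and planned analyses are unchanged; the stated power becomes less favourable for the ICER and, if the test is two-sided, for the rates too.

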**Methods/Design:**

A multicenter, open-label randomized controlled trial (RCT) will be conducted in which 20 French obstetrics and gynecology centers will recruit eligible pregnant women at less than 20 weeks gestation with singleton pregnancy and with a low-risk factor for preterm birth. Interventions will include a) an experimental group that will receive a systematic rapid screen-and-treat program from a point-of-care analysis using a molecular quantification method and b) a control group that will receive usual care management. Randomization will be in a 1:1 allocation ratio. The primary endpoint that will be assessed over a period of 12 months will be the incremental cost-effectiveness ratio (ICER) expressed as cost per avoided preterm birth before 37 weeks. Secondary endpoints will include ICER per avoided preterm birth before 24, 28 and 32 weeks, obstetrical outcomes, neonatal outcomes, rates of treatment failure and recurrence episodes for positive women. Uncertainty surrounding these estimates will be addressed using nonparametric bootstrapping and represented using cost-effectiveness acceptability curves. A total of 6,800 pregnant women will be included.

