#### Inclusion and exclusion criteria

The details of the inclusion and exclusion criteria are provided in Table 2. The main inclusion criteria are that women must have less than 20 weeks of gestation, with singleton pregnancy, they must be symptomatic or nonsymptomatic with regard to their diagnosis of BV, and they must not have high-risk factors of preterm birth. The main exclusion criteria are having known conditions at the time of recruitment that have either increased risk of spontaneous preterm birth (previous preterm birth, uterine malformation, or multiple pregnancy) or that may need preterm delivery due to medical indication: hypertension, diabetes, fetal malformation, increased risk for preeclampsia (or other conditions that the investigators may consider).

**Table 2 Tab2:** Selection criteria

Inclusion criteria
Woman ≥ 18 years of age
Woman less than 20 weeks of gestation
Woman with singleton pregnancy
Woman without history of preterm birth or late miscarriage
Woman with low-risk factor of preterm birth (absence of diabetes, systemic lupus erythematosus, treated hypertension, fetal malformation, cervical conization, or multiple pregnancy)
Woman affiliated to or beneficiary of a social security system
Woman who have signed written informed consent
Exclusion criteria
Woman more than 20 weeks of gestation
Minor woman or woman deprived of their freedom by a court/administrative decision or woman under legal protection
Woman who present high-risk factor of preterm birth or late miscarriage
Woman with extrauterine pregnancy
Woman with non-evolutive pregnancy
Woman who have received antibiotic treatment in the week before inclusion
Woman misunderstanding the written and spoken French language
Subject participating in another biomedical research protocol

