### Recruitment

Eligible women will be invited to take part in the study during a routine prenatal consultation planned in the first trimester of their pregnancy. The women who meet all the inclusion criteria will be randomized into one of the two groups after completing the informed consent form.

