### Cost-effectiveness analysis

Incremental cost-effectiveness ratios (ICER) will be used to compare the cost and effectiveness of the experimental strategy with usual care. The ICER is the ratio of the difference between groups in costs to the difference in effectiveness. The difference in effectiveness equals the number of preterm births averted and is calculated as the number of preterm births in the screening group minus the number of preterm births in the control group. Thus, the ICER provides information on the potential acceptability of the intervention for decision makers. The costs perspective taken in our economic analysis is that of the healthcare payer. The time horizon started from the first prenatal consultation before the 20 weeks of gestation and ended at 6-months of age or death. The healthcare costs included are those that are likely to differ across the intervention and control groups. In our study, these costs are those associated with: screening using the point-of-care procedure (quantitative molecular analysis), control vaginal swabs for positive women, antibiotic treatments, antenatal hospital admissions, physicians’ consultations, management of complications, as well as neonatal costs for full term infants and preterm infants. Unit costs for health service use will be estimated using data from the French National Hospital Database (Programme de médicalisation des systèmes d’information, PMSI) and the National Tariff. Treatment costs were obtained from the French register of pharmaceutical specialties, an online database of information on healthcare products. The cost of the POC analysis using quantitative real-time PCR (qPCR) will be calculated using micro-costing technique, which is particularly well suited to evaluating the cost of an emerging technique [27]. The volume of resources used will be determined by direct observation of each stage of each testing procedure. Fixed and variable costs will be included. All resources will be valued in 2015/2016 euros, and the 12-month trial means there is no requirement to apply discounting. As the cost of preterm birth differs significantly according to the gestational age at birth [28–30], we will attempt to address this issue by calculating an ICER for specific birth gestational ages. Probabilistic sensitivity analyses, using the non-parametric bootstrap method, will be carried out to generate mean expected ICERs and to determine whether uncertainty or variation in the data used affect the ICERs [31]. In addition, cost-effectiveness acceptability curves were constructed to represent decision uncertainty surrounding cost-effectiveness estimates [32].

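### The 12-month maximum participation is too short for first-trimester recruitment with an assessment and cost horizon at 6 months after delivery

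*Protocol article*

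**What the plan says.** All references are to the protocol article.

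- **Sample size** limits each woman's time in the study: "The maximal period of participation for the included women is 12 months".
- **Abstract, Methods/Design** uses the same length for the main result: "The primary endpoint that will be assessed over a period of 12 months". **Cost-effectiveness analysis** gives a 12-month trial as the reason for not discounting.
- **Recruitment** invites women "during a routine prenatal consultation planned in the first trimester of their pregnancy". Table 2 sets the outer limit: "Woman less than 20 weeks of gestation". No lower limit is given.
- **Data collection and follow-up** sets T3 at 6 months after delivery. Table 3 says that mothers then complete a questionnaire to "record all health outcomes of their infant and associated health service use". The text of that section describes the same self-report as covering the 6 months after the initial hospital stay, which is a later end point.
- **Cost-effectiveness analysis** starts the horizon at the first prenatal consultation before 20 weeks and says that it "ended at 6-months of age or death".
- **Statistical analysis** plans multiple imputation where possible, with a sensitivity analysis.

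**The concern.** The participation limit and the cost horizon describe the same follow-up but give different lengths. The 12 months cannot be dismissed as a passing remark: it is called a maximum, the abstract attaches it to the primary endpoint, and the discounting decision rests on it. A reader cannot tell whether 12 months from inclusion or 6 months of age governs the costs in the primary incremental cost-effectiveness ratio (ICER).

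T3 is the planned self-report of infant service use after the initial stay, collected in one questionnaire. If a site closed a woman's participation at 12 months, that whole record could be lost, not only its last weeks. Time from inclusion to T3 grows with gestational age at birth, and birth before 37 weeks is the effectiveness measure. An enforced limit would therefore make missing cost data depend on the outcome.

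**Working it through.** **Inputs.** Limit: 12 months = 52.18 weeks (Sample size). T3 and end of costing: 6 months = 26.09 weeks after birth (Data collection and follow-up; Cost-effectiveness analysis). Inclusion: first trimester by plan, under 20 weeks by eligibility (Recruitment; Table 2). Assumptions: gestational weeks count from the last menstrual period, and the first trimester ends at about 13 to 14 weeks.

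**Formula.** Weeks needed = (week of birth − week of inclusion) + 26.09. T3 fits if this is at most 52.18, that is, if birth comes no more than 52.18 − 26.09 = 26.09 weeks after inclusion.

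**When does the stated 12 months come out?** For a 40-week birth, inclusion must be at 40 − 26.09 = 13.9 weeks or later. Inclusion at 14 weeks needs 26 + 26.09 = 52.09 weeks, or 11.98 months. The stated maximum thus fits a 40-week birth only when inclusion is at or beyond the end of the planned recruitment window.

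| Inclusion (weeks) | Latest birth that fits (weeks) | Months needed, birth at 34 weeks | Birth at 37 weeks | Birth at 40 weeks |
|---|---|---|---|---|
| 8 | 34.1 | 11.98 | 12.67 | 13.36 |
| 10 | 36.1 | 11.52 | 12.21 | 12.90 |
| 11 | 37.1 | 11.29 | 11.98 | 12.67 |
| 12 | 38.1 | 11.06 | 11.75 | 12.44 |
| 13 | 39.1 | 10.83 | 11.52 | 12.21 |
| 14 | 40.1 | 10.60 | 11.29 | 11.98 |
| 20 | 46.1 | 9.22 | 9.91 | 10.60 |

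For a 40-week birth, the overrun is (40 − 13 + 26.09) − 52.18 = 0.9 weeks for inclusion at 13 weeks and (40 − 8 + 26.09) − 52.18 = 5.9 weeks for inclusion at 8 weeks. The longest case tried, inclusion at 6 weeks and birth at 42, needs 36 + 26.09 = 62.09 weeks, or 14.3 months.

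**How the overrun relates to the outcome.** Within a row, later birth means longer participation. The cut coincides with 37 weeks only for inclusion near 11 weeks (37 − 26.09 = 10.9). With inclusion at 8 weeks, preterm births after 34.1 weeks also overrun. With inclusion at 12 or 13 weeks, term births up to 38.1 or 39.1 weeks fit.

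**Possible size of the effect on incremental cost.** The planned preterm rates are 4.3% and 3.0%, so the arms differ by 0.013 in the proportion of term births. Suppose that the limit were enforced, that only term infants lost data, that each lost the same amount c in both arms, and that the loss counted as zero cost. Incremental cost would then shift by 0.013 × c, and the ICER at the planned effect by (0.013 × c) / 0.013 = c. The article gives no value for c, so a range is assumed:

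| Assumed loss c per term infant | Shift in incremental cost (planned: EUR 230) | Shift per preterm birth avoided, against EUR 22,500 |
|---|---|---|
| EUR 100 | EUR 1.3 | EUR 100 (0.4%) |
| EUR 500 | EUR 6.5 | EUR 500 (2.2%) |
| EUR 1,000 | EUR 13 | EUR 1,000 (4.4%) |

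**The case against.** The best defence is that 12 months is a rounded duration at the end of a sample-size paragraph. The sections that define the data set T3 for every participant and costing to 6 months of age, and none stops data collection earlier. Women included at 14 to 20 weeks fit even with a 40-week birth. This stands: data loss follows only if the limit is allowed to override T3.

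A reader might go further and infer that cost data will be missing for term births and complete for preterm births, so that term-infant cost is understated and the saving per preterm birth avoided exaggerated. The article does not support that, for four reasons:

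- The cut moves with inclusion week, so some late-preterm births overrun and many early-term births fit.
- If the 6 months are counted from discharge, as one sentence has it, preterm infants with long stays overrun as well. The Discussion allows neonatal care of up to 6 months for very preterm births.
- Multiple imputation is planned. The overrun is determined by week of inclusion and week of birth, both of which should be on record, and later recruits with term births would supply observed T3 data. Understatement requires missing costs to count as zero; an imputation leaning on preterm infants would err the other way.
- The arms differ by only 1.3 points in preterm births, so most of any loss would be common to both.

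The defence does not remove the contradiction itself. A figure called a maximum should cover an ordinary first-trimester recruit with a 40-week birth, and this one does not.

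**Conclusion.** The 12-month maximum is wrong as written. With first-trimester inclusion at 8 to 13 weeks and birth at 40 weeks, T3 and the end of the cost horizon fall 12.2 to 13.4 months after inclusion. The abstract and the discounting statement carry the same error.

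The consequence for the data is conditional. If the limit were enforced, T3 would be lost more often the later the birth, and missingness would be related to the effectiveness outcome. How many women this would affect cannot be computed, because the article gives no distribution of inclusion or birth weeks. The direction of bias is open. The shift in incremental cost is probably small: EUR 1.3 to 13 against EUR 230 for assumed losses of EUR 100 to 1,000 per term infant. The choice not to discount would hardly change the result, since only the last weeks fall beyond 12 months; it is the stated premise that fails.

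The timing figure and the consent form are not at hand and may state the period differently.

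**What to change.** - **Sample size:** state that participation lasts until 6 months after delivery, with a maximum of about 13 to 14.5 months from inclusion, depending on the earliest inclusion week allowed.
- **Cost-effectiveness analysis:** make 6 months of age (or death) the governing horizon for all infants, whatever their gestational age at birth, and restate the reason for not discounting without the 12-month premise.
- **Data collection and follow-up:** replace the period counted from the initial hospital stay so that it agrees with T3 and the 6-months-of-age horizon.
- **Abstract:** replace the 12-month assessment period for the primary endpoint in the same way.
- **Consent form:** check that it carries the same period, and amend it if it does not.

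This is a short wording amendment. If T3 is already scheduled for every woman, it adds no follow-up. If sites have been working to the 12-month limit, the last participant's end date moves by at most about 2 to 2.5 months.
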